# The effect of a sit-stand workstation intervention on daily sitting, standing and physical activity: protocol for a 12 month workplace randomised control trial

**DOI:** 10.1186/s12889-015-1506-y

**Published:** 2015-02-15

**Keywords:** Health, Multi-component intervention, Physical activity, Process evaluation, Randomised control trial, Sedentary behaviour, Sit-stand workstation, Sitting, Standing, Workplace

## Abstract

**Background:**

A lack of physical activity and excessive sitting can contribute to poor physical health and wellbeing. The high percentage of the UK adult population in employment, and the prolonged sitting associated with desk-based office-work, make these workplaces an appropriate setting for interventions to reduce sedentary behaviour and increase physical activity. This pilot study aims to determine the effect of an office-based sit-stand workstation intervention, compared with usual desk use, on daily sitting, standing and physical activity, and to examine the factors that underlie sitting, standing and physical activity, within and outside, the workplace.

**Methods/Design:**

A randomised control trial (RCT) comparing the effects of a sit-stand workstation only and a multi-component sit-stand workstation intervention, with usual desk-based working practice (no sit-stand workstation) will be conducted with office workers across two organisations, over a 12 month period (N = 30). The multicomponent intervention will comprise organisational, environmental and individual elements. Objective data will be collected at baseline, and after 2-weeks, 3-months, 6-months and 12-months of the intervention. Objective measures of sitting, standing, and physical activity will be made concurrently (ActivPAL3™ and ActiGraph (GT3X+)). Activity diaries, ethnographic participant observation, and interviews with participants and key organisational personnel will be used to elicit understanding of the influence of organisational culture on sitting, standing and physical activity behaviour in the workplace.

**Discussion:**

This study will be the first long-term sit-stand workstation intervention study utilising an RCT design, and incorporating a comprehensive process evaluation. The study will generate an understanding of the factors that encourage and restrict successful implementation of sit-stand workstation interventions, and will help inform future occupational wellbeing policy and practice. Other strengths include the objective measurement of physical activity during both work and non-work hours.

**Trail registration:**

Clinicaltrials.gov identifier NCT02172599, 22nd June 2014.

## Background

Sedentary behaviour (taken from the Latin term *sedere*; to sit) has been operationally defined as any activity that involves an energy expenditure of ≤ 1.5 METS (metabolic equivalents), performed in seated or lying position [1]. Emerging research evidence identifies sedentary behaviour as a risk factor for negative health outcomes in the adult population; this risk is distinct and independent from risk associated with physical inactivity [2-4]. A lack of breaks in sedentary time is also related to metabolic disease risk [5,6]. For example, lipoprotein lipase is regulated differently following sedentary behaviour and physical activity; whilst a reduction in LPL activity occurs only in oxidative muscle fibres following sedentary behaviour, physical activity promotes increased LPL activity in glycolytic muscle fibres [7]. Further, a recent intervention study found that self-reported sitting time was significantly associated with a component of DNA; telomere length [8] Shortening of telomeres is associated with ageing and onset of disease [9]. This evolving evidence raises the question, “What should the person who sleeps an average of 8 hours per day [and is physically active for 30 minutes per day] do for the remaining 15.5 hours?” [10]. Thus, research and policy guidelines, such as the UK’s ‘Start Active, Stay Active’ policy are now promoting both increases in physical activity and decreases in sedentary behaviour, stating adults should “*minimise the amount of time spent being sedentary (sitting) for extended periods*” [11].

Physical activity has been defined as “any bodily movement…that results in energy expenditure” [12]. There is a well-established body of evidence supporting the health benefits of physical activity [13]. However, physical activity is a complex behaviour; participation differs among different socio-economic groups and in the contexts and environments that contribute to health inequalities [14-16]. In the UK, it is estimated that over 73% of working age adults were engaged in full time or part time employment between April 2014 and June 2014 [17] and that adults spend an average of 60% of the working day at the workplace [18]. Thus, the workplace is an ideal setting for promoting physical activity and reductions in sitting. The office is a particularly important workplace setting, given the high proportion of sedentary time in desk-based office workers. For example, an observational study measured objectively the sedentary behaviour and physical activity of 50 office-based employees for 7 consecutive days; it found that, on average, 81.8% of working hours were spent engaged in sedentary behaviours, compared to 68.9% of non-work hours. Additionally, there were fewer breaks in sedentary time, and less light-intensity activity, during working hours than during non-working hours (p < 0.001) [19]. This suggests that office-workers are more sedentary and less active during work than outside work and thus the office-based workplace is a crucial context for intervention to promote increases in physical activity and reductions in prolonged sitting. In desk-based office occupations, prolonged sitting is likely to occur in the context of travelling to work and participating in meetings, however, approximately two-thirds of workplace sitting time is spent at a desk [20].

One response to reducing sitting time in the workplace is the installation of sit-stand workstations. Sit-stand workstations offer height-adjustable desk equipment for computer screens and keyboards allowing employees a choice of desk-based working positions. Several studies have examined the contribution of sit-stand workstations to a range of sedentary behaviour, health and productivity outcomes. Previous sit-stand workstation intervention studies have seen varying reductions in the amount of time spent sitting, ranging from 66 minutes to 143 minutes per day [21]. A recent meta-analysis of activity-permissive workstations revealed that the reduction in sedentary behaviour is greater in interventions that incorporate a change to the working environment (i.e. an activity-permissive workstation), than interventions that do not [22]. Physiological research shows that using a sit-stand workstation for 185 minutes, immediately after eating, can reduce post-prandial glucose excursion by 43% [23]. A recent review of empirical studies examining the relationship between sit-stand workstations and a range of measures of productivity revealed that whilst the majority of studies show that using a sit-stand workstation had no influence on productivity, no studies showed a reduction in productivity [24]. In line with an ecological approach to behaviour change [25], initial research has shown that greater reductions in sitting time (56 min/8-hour workday) can be achieved as a result of a multi-component sit-stand workstation intervention (incorporating individual and organisational level components) compared to receiving a sit-stand workstation alone [26]. However, this needs to be replicated over a prolonged time-period (e.g. 12 months), on outcomes related to physical activity (distinct from sitting, standing and stepping). Whilst the feasibility of using sit-stand workstations has been qualitatively explored with desk-based office workers [27], outcome-focused studies dominate this research area. Understanding of the social processes that encourage and restrict standing and physical activity in the workplace is required. The absence of systematic and rigorous process evaluations of sit-stand workstation interventions will impede the wider adoption of sit-stand workstations across organisations [28,29].

### Aims

The primary aim is to determine the effect of a 12 month multi-component sit-stand workstation intervention, incorporating organisational, environmental and individual level strategies, on physical activity within the workplace (primary outcome). Secondary aims are to: determine the effect of the sit-stand workstation intervention on physical activity outside of the workplace (secondary outcome), and to determine whether the multi-component intervention is more effective than the sit-stand workstation provision alone. The process evaluation will examine the factors that influence sitting, standing and active behaviours in the workplace.

## Methods/Design

### Study design

An RCT comparing the effects of a sit-stand workstation only and a multi-component sit-stand workstation intervention, with usual office-based working practice (no sit-stand workstation) will be implemented. The study will be conducted with office workers across two organisations according to Cochrane recommendations [30], with ‘individuals’ being the unit of randomisation. The design employs two intervention arms: (1) a multi-component sit-stand workstation intervention (SS-MC); and (2) sit-stand workstation only (SS-O). A control arm (CG) for usual desk-based working practice (no sit-stand workstation) will also be included. Objective data collection will take place at 5 time-points over the course of 12-months: baseline (approximately one month before desk installation), and then post-installation at 2-weeks, 3-months, 6-months and 12-months. See Figure 1 for an overview of the study design and major study components. Ethics approval has been granted by Brunel University London local research ethics committee. All participants will receive a participant information sheet, which details their ethical rights, and provide written informed consent. The conduct of this study will follow the CONSORT guidelines (http://www.consort-statement.org/).

**Figure 1 Fig1:**
[figure not shown]
**Study overview including recruitment and study design, intervention procedures and data collection.**

### Recruitment

#### Recruitment of organisations and study sites

Two organisations, Macmillan Cancer Support and Public Health England (PHE) will provide use of workplaces (one per organisation) and employees as participants for the study. Macmillan Cancer Support is a charitable organisation that provides support for people living with and affected by cancer. The UK Office based in Central London, UK is the worksite selected for this study. Public Health England is a governmental organisation responsible for protecting and improving the nation’s health and wellbeing, and reducing health inequalities. One PHE worksite in central London will be used in this study.

#### Recruitment of participants

Participants will be recruited via internal advertisement. At PHE, this will involve an email sent to all employees at the chosen worksite. At Macmillan Cancer Support, this involves an email sent to all employees at the chosen worksite, alongside their standard internal communication channels (Yammer page, posters). All potential participants will be required to attend a 45–60 minute recruitment workshop at their organisation. If they are unable to attend a workshop, they must engage in a 30 minute telephone conversation with the lead researcher to discuss the study requirements to be eligible to formally apply to take part in the research.

Potential participants will be invited to complete an expression of interest form that asks questions regarding age, gender, ethnicity, and disability status, as well as what interests them about sit-stand workstations, and whether they, or a close friend or family member, have ever had a cancer diagnosis*.**Funding acquired for this study requires that some of the participants have been affected by cancer; via a personal cancer diagnosis and/or a close friend or family member being diagnosed with cancer.*

#### Eligibility criteria

Participants must be full-time employees on a permanent or fixed term contract until the anticipated study end date, with no plans to leave the organisation, or be absent for an extended period (≥4 weeks). Participants must engage primarily in desk-based office-work, be present at the worksite ≥ 4 days a week, and must be at least 18 years of age. Participants must not have engaged in standing-based desk work in the four weeks prior to baseline data collection. Participants must not have been advised to avoid prolonged standing by a health professional; or be unable to stand.

Certain work teams at one of the participating organisations are excluded owing to the sensitivity of their work and current desk configuration; the current desks would need to be significantly adapted to accommodate the sit-stand equipment.

#### Participant selection

Of the potential participants that attend a recruitment workshop and complete the expression of interest form, those that do not meet the eligibility criteria will be excluded immediately. Thirty participants will then be selected strategically to take part in the research; selection will ensure the sample is representative of the range of characteristics on the expression of interest form (see above). The participants that are not selected will be put on a waiting list in case of drop-outs.

### Randomisation

Participants will be allocated randomly to one of three arms using an online randomisation programme (www.randomizer.org). Participants from the two participating organisations will be randomised separately, to achieve an equal number in each study arm in both organisations. Given the nature of the intervention, i.e. the fact that participants may or may not receive a sit-stand workstation, it will not be possible to blind participants or researchers to arm allocation. However, concealment allocation will be implemented [27].

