##### Individual level procedures

Participants in the SS-MC arm will receive four 5–10 minute telephone calls (before installation of the sit-stand workstation, and at weeks 3, 10 and 19) from the lead researcher who is experienced in motivational interviewing, as a method for “enhancing intrinsic motivation to change, by exploring and resolving ambivalence” [39]. These telephone calls will engage participants in conversations related to the sit-stand workstations and physical activity that will follow the principles of engaging, guiding and evoking to motivate and support participants to reduce their inactivity and increase activity, primarily at the workplace.

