#### Outcome data

Primary outcomes are: daily time spent sitting, standing, in light and moderate-vigorous physical activity, the average number of sit-stand transitions per hour, number of prolonged sitting bouts ≥30 min, and total physical activity energy expenditure during work hours. Secondary outcomes will be the same, but over the course of the entire day (see Table 1)*.* These will be measured at baseline (approximately one month before sit-stand workstation installation) and four subsequent time-points following workstation installation; two-weeks, 3-months, 6-months and 12-months. Each data collection period will be 7-days. Sitting, standing and sit-stand transitions will be assessed using an ActivPAL3™ micro monitor (PAL Technologies Limited, Glasgow, UK) and light, moderate and vigorous physical activity will be assessed using an accelerometer (ActiGraph GT3X+, ActiGraph, Pensacola, FL, USA). The ActivPAL3™ provides accurate measures of sitting time and sit-to-stand transitions per hour and sit-stand transitions, when compared to direct observation in office-based free-living environments [41,42]. The ActivPAL3™ will be worn continuously on the centre of the right thigh, following insertion into a nitrile sleeve and wrapping in a waterproof dressing. Participants will be given extra materials to change the dressing when required. Participants will be requested to wear the monitor continuously for each 7-day data collection period. The ActiGraph GT3X+ is a tri-axial accelerometer that accurately classifies physical activity intensity in free-living environments [43]. It will be worn on the hip via an elastic belt during waking hours only, excluding time spent engaged in water-based activities. Participants will be asked to record non-wear time of both monitors, and time spent at the workplace for all 7-day data collection periods.

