### Statistical methods

Two-way repeated measures ANCOVA will be conducted using IBM SPSS Statistics 20 to compare the outcome measures between study arms and across the intervention (between data collection time points). Relevant covariates will be controlled for, including body mass index.

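### The statement that researchers cannot be blinded is too broad: its reason does not reach monitor-file processing or analysis, where the open ActiGraph non-wear rule leaves room for arm-aware choices

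*Protocol article*

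**What the plan says.** Under Randomisation, the protocol article opens its blinding statement with a reason: "Given the nature of the intervention, i.e. the fact that participants may or may not receive a sit-stand workstation". It concludes that "it will not be possible to blind participants or researchers to arm allocation". The word researchers is not limited to any role. The one safeguard then named is that "concealment allocation will be implemented".

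Under Outcome data, the article states: "Primary outcomes are: daily time spent sitting, standing, in light and moderate-vigorous physical activity", with further items, all during work hours. The activity-intensity part comes from the ActiGraph: "light, moderate and vigorous physical activity will be assessed using an accelerometer". Every measure in Table 1 is derived from one of the two monitors. Work time and non-wear rest partly on self-kept records: "Participants will be asked to record non-wear time of both monitors, and time spent at the workplace".

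The section on non-wear time criteria does not fix the ActiGraph rule. The rule is to be worked out from accepted standards and from looking at the data, with the ActivPAL output as a comparator. The same section acknowledges that the choice affects how many participants remain and what values the outcomes take.

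Under Individual level procedures, the calls to the multi-component arm come "from the lead researcher who is experienced in motivational interviewing". Statistical methods adds: "Relevant covariates will be controlled for, including body mass index".

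**The concern.** The reason given concerns who sees, or hears about, the workstation. File processing and model fitting are later steps on downloaded data, and a person who has not met the participants can carry them out under neutral codes. By declaring blinding impossible for researchers as a whole, the plan gives up a protection that is available at this stage.

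The loss matters because at least one processing rule is left to be chosen with the data in view. If the people who choose it know the arms, they can see how each candidate rule moves the arm comparison. With 30 participants in three arms (30 / 3 = 10 per arm), a rule that removes wear time, or removes participants, leaves little data to absorb the effect. The Abstract and the Discussion present objective measurement as a strength. That strength depends on the steps between the monitor and the analysed value being protected as well.

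**Working it through.** The document gives no figure for this point, so there is nothing to recompute. The Sample size section states that no formal power analysis was done. The check sets the relevant sections side by side.

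1. **Scope of the statement.** Randomisation names participants and researchers and excepts no role. This is a positive statement about what can be done. It is not merely silence on a detail.

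2. **Reach of the reason, role by role.**
   - Participants: it applies, since they know whether they have a workstation.
   - The lead researcher: it applies. This person makes the calls to the multi-component arm (Individual level procedures) and spends about 12 working days in each of three phases at each worksite (Ethnographic participant observation).
   - Other on-site staff: it applies.
   - A person who receives monitor and log files under neutral codes, or who fits models with arms labelled A/B/C: it does not apply. Nothing about receiving a workstation requires this person to know the arm.

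3. **Does the named safeguard cover the gap?** No. Allocation concealment protects the assignment up to the moment of allocation. It does nothing for processing or analysis afterwards.

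4. **Is a consequential choice made after the data are seen?** Yes, for the ActiGraph non-wear rule. The section on non-wear time says so, and says that the choice affects sample size and outcomes.

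5. **Which outcomes does that choice reach?** It reaches the ActiGraph outcomes. These include light and moderate-vigorous activity during work hours, which are primary. The document states no data-dependent rule for the ActivPAL outcomes (sitting, standing, transitions and prolonged bouts): the monitor records bouts and proprietary software processes them. The ActiGraph intensity cut-points are fixed in advance and are not at issue.

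6. **Does the document say that the choice is made with knowledge of arm?** No. It does not say who processes the files or whether arm labels are attached. Arm awareness at this stage is inferred from the unrestricted statement under Randomisation.

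Steps 1 to 5 show that the stated impossibility is false for file processing and analysis, and that the opening reaches at least some primary outcomes. Step 6 limits the conclusion to what can happen.

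**The case against.** The strongest reply is that researchers, under a heading about randomisation and with a reason tied to the workstation, naturally means the people running the trial on site. On that reading the article does not speak about analysts, and masking of analysts is a detail that a condensed article may leave to a fuller document. The reading is possible. But the text sets no such limit, and a later plan that provided for masked processing would contradict the sentence as written. The wording needs correcting on either reading.

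Second, the non-wear rule appears to be a single rule for the whole data set, judged against the ActivPAL output. It does not appear to be a series of person-by-person decisions. This stands and lowers the risk. It does not remove it, because one common rule can still be chosen after seeing which arm it favours.

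Third, masking would be imperfect. Standing patterns may suggest who has a desk, and the logs are kept by participants who know their arm. Both points stand and are costs of the remedy.

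A reader might go further and infer that arm-aware choices do enter all the primary outcomes, through dropped ActivPAL days, conflicts between log and monitor, or selected covariates. The documents do not support this. They describe no ActivPAL day-dropping and no procedure for resolving log conflicts, and a statistical analysis plan may well fix the open covariate list. A reader might also want the possible bias in minutes. Any such figure would need assumed values for the days dropped, their deviation and the number of people affected in one arm, and the document supplies none of these.

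**Conclusion.** The point holds in a limited form. The statement under Randomisation is broader than its reason supports: blinding is not ruled out for those who process monitor files or run the analysis. Because the ActiGraph non-wear rule is left open until the data are seen, arm-aware choices can enter at least the light and moderate-vigorous activity primary outcomes. The document does not show that they do.

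No magnitude can be estimated. The conclusion rests on two readings: that researchers is meant without limit of role, as written, and that nobody masked to arm has been assigned to file processing, which the article neither states nor denies. This is a cheap improvement that guards against bias. It is not evidence that bias has occurred.

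**What to change.** - Reword the Randomisation statement so that it covers only participants and staff who deliver the intervention or work on site, and state that monitor-file processing and statistical analysis are masked to arm.
- Have an existing team member who does not deliver the intervention relabel the monitor and log files with neutral codes and hold the key.
- Fix the non-wear rule, the other processing rules and the covariate set, and run the main models with arms coded A/B/C, before the key is opened.

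The cost is a recoding list, a short change of wording and a slight delay. It assumes that the team includes someone who does not deliver the intervention, which the article does not describe. According to Trial status, data collection was unfinished at manuscript submission, so the change could still be made then.

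Two limits should be stated openly. Masking of desk versus no desk will be partial, because standing patterns may reveal it. The comparison of the two workstation arms is better masked, since both have desks. Coding the files also does nothing about work-time and non-wear records kept by participants who know their arm.
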